#### Data management

Patient characteristics and operative details will be captured in the ACHQC database, accessed using an assigned username and password. Treatment arm allocation, postoperative complications, CT results, and patient-reported quality of life scores will be collected in REDCap®, a secure electronic database accessed by the investigator and designated study team members using an assigned login and password. Only the principal investigator, research coordinators, and biostatisticians will have access to patient data for routine data quality assessments and data analyses. All electronic records pertaining to the clinical study will be password-protected, and only approved study members listed in the Institutional Review Board (IRB) protocol will have password access.

### Statistical methods

#### Statistical methods for primary and secondary outcomes

All analyses will be conducted on intention to treat basis (ITT). An ACHQC statistician will perform analyses from all participating centers and will require access to identifiable data. A DUA will be executed prior to sharing of PHI. Patient characteristics and operative comparisons will be summarized by the treatment group. Any departures from ITT will be documented and reported.

Participants’ clinical and demographic characteristics will be summarized by treatment arms. Differences between two groups will be assessed using Wilcoxon rank sum tests for continuous variables and Chi-square or Fisher’s exact tests for dichotomous variables. One-sided p-values less than or equal to 0.05 will be considered statistically significant.

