### Sample size

Using an alpha of 0.05, a power of 0.90, and determining a 24-h difference in length of stay, the necessary sample size is 86 patients in each arm, yielding a total of 172 patients. Estimating 10% attrition at 30 days, 200 patients would be needed, 100 patients enrolled in each arm.

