### Primary analysis

The primary outcome for this study is length of stay measured in hours. Length of stay will start at the time of surgery start and will end when discharge order is placed. Analysis will be performed using the intent to treat analysis. The comparison in length of stay between two groups will be conducted by using two-sided Wilcoxon ranked sum test with significance level of 0.05. Two sample student’s t-test with log-transfomation would also be considered if we are interested to interpret the length of stay with mean and standard error. Per-protocol analysis will also be done if there’s excessive non-adherence or switching groups during the study. Tipping point analysis will be performed when loss of follow up is anticipated.

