### Secondary analyses

NRS 11, PROMIS, HerQles and EuraHS scores will be collected pre-operatively as baseline scores. The difference in mean scores at 30 days and 1 year between two groups will be compared using linear mixed effect models that include the baseline measurement, group by time interaction as fixed effect, and repeated measurements and possibly the surgeon as random effects. The main effect of group will be omitted from the model to force a common baseline effect across groups. The planned linear mixed effect models allow patients to remain in the analysis even when they are missing follow up data. If the distributional assumptions are not met, then alternate generalized linear mixed effect models will be considered.

OR time and Cost would be compared by using the two-sample Wilcoxon ranked sum tests and the cost data would possibly be re-scaled.

SSI, SSO and SSOPI, along with other complications, re-admission and recurrence will be compared by using two sample Chi-square or Fisher’s exact tests.

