## Discussion

Robotic retromuscular hernia repairs have been shown to be safe, effective, and potentially beneficial to patients compared to open techniques [3, 5, 6, 8, 17, 18], but still lacking high quality data. Recently, a randomized trial comparing robotic to open abdominal wall reconstruction for ventral hernias was published [4]. There are some important limitations to this trial including the primary outcome being composite wound morbidity in early post-operative period [1]. These cohort of patients have a planned long term follow up which will be interesting to see if any benefit exists to having a minimally invasive approach to abdominal wall reconstruction. This addition of a randomized trial adds significant value to the current body of literature in the field.

Other retrospective data currently exists. A large case control study found no difference in intraoperative complications between robotic and open TAR (8.9% vs 16.5%, *P* = 0.137) and an 8.9% conversion rate to open. Yet other retrospective series highlights lower estimated blood loss, but without difference in transfusion requirements [6]. Carbonell and colleagues published a 2:1 propensity score matched cohort study of robotic and open retromuscular ventral hernia repairs from the ACHQC in 2018 [3]. This data demonstrated a significantly higher SSO incidence in the robotic group, which was driven by a higher rate of seromas not requiring intervention. There was noted to be a decreased hospital length of stay. This benefit seems to be a recurring consistent advantage of the robotic approach when compared to open retromuscular ventral hernia repairs in retrospective studies [1, 3, 5, 6]. The remaining studies published have been case series, systematic reviews, or large registry data, all of which have significant limitations and inherent bias due to trial design [2].

Based on the available literature, we designed a randomized, double-blinded trial comparing robotic to open ventral hernia repairs using retromuscular techniques. We hypothesized that robotic retromuscular repairs will be superior to open by reducing length of stay by at least 24 h compared to open repairs. This will provide high-quality data to help surgeons make important clinical decisions regarding the care they provide for patients.

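### The general methods section uses a one-sided 0.05 threshold with no stated direction, against a two-sided 0.05 test for length of stay; the secondary comparisons are the most exposed

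*Protocol article*

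**What the plan says.** All places are in the protocol article.

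- *Statistical methods for primary and secondary outcomes*: after naming "Wilcoxon rank sum tests for continuous variables and Chi-square or Fisher’s exact tests for dichotomous variables" for differences between the groups, the section ends "One-sided p-values less than or equal to 0.05 will be considered statistically significant". It gives no direction.
- *Primary analysis*: length of stay is compared by a "two-sided Wilcoxon ranked sum test with significance level of 0.05". The section on non-adherence and missing data repeats this. A log-transformed t-test is mentioned as a possible alternative, without its own sidedness.
- *Secondary analyses*: "OR time and Cost would be compared by using the two-sample Wilcoxon ranked sum tests". Wound events and other complications, along with "re-admission and recurrence will be compared by using two sample Chi-square or Fisher’s exact tests". Patient-reported scores go into mixed models. No sidedness or significance level is given for any of these.
- *Sample size*: "Using an alpha of 0.05, a power of 0.90" and a 24 h difference give 86 per arm, raised to 100 per arm for attrition. Neither the sidedness of the alpha nor an SD is stated.
- *Discussion*, on an earlier propensity-matched registry comparison: "This data demonstrated a significantly higher SSO incidence in the robotic group". The article adds that seromas needing no intervention drove this excess.

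**The concern.** Two thresholds are stated, and the heading over the one-sided rule includes the primary outcome. If that rule were applied to length of stay, a result favouring robotic repair with a two-sided p between 0.05 and 0.10 would count as significant under one section and not under the next.

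For secondary outcomes nothing competes with the one-sided sentence, yet it cannot be applied as written. A one-sided p-value needs a direction, and the article gives a directional hypothesis only for length of stay, the one outcome that is explicitly tested two-sided. A standard chi-square test is non-directional. An analyst would have to supply a direction for every wound, readmission, recurrence, cost and quality-of-life comparison, and nothing says when that choice is made.

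The choice matters most for wound events. The hypothesis favours robotic repair, while the article itself cites data with more surgical site occurrences (SSO) after it.

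**Working it through.** **1. Error rates under each rule (normal tail areas)**

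| Rule | Critical z | False claim in one given direction | Total false claims |
|---|---|---|---|
| Two-sided 0.05 | 1.960 | 0.025 | 0.05 |
| One-sided 0.05, direction fixed in advance | 1.645 | 0.05 in that direction, 0 in the other | 0.05 |
| One-sided 0.05, direction chosen after seeing the data | 1.645 | 0.05 | 0.10 |

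As a check, 20,000 null trials were simulated with the Wilcoxon test at 86 per arm and log-normal stays. Rejection rates were 0.049 (one-sided, fixed direction), 0.047 (two-sided, of which 0.024 in the robotic-benefit direction) and 0.098 (direction chosen afterwards).

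**2. What a benefit-directed test would miss**

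This is an illustration only. The SSO rates of 15% open and 30% robotic are assumptions, with n = 86 per arm and pooled rate 0.225.

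- SE under the null = √(0.225 × 0.775 × 2/86) = 0.0637.
- SE under the alternative = √((0.15 × 0.85 + 0.30 × 0.70)/86) = 0.0626.
- Two-sided test: Φ((0.15 − 1.960 × 0.0637)/0.0626) ≈ 0.66.
- One-sided test for robotic benefit: Φ((−0.15 − 1.645 × 0.0637)/0.0626) ≈ 0.00002.

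**3. The plan's 86 per arm**

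Inputs from *Sample size*: difference 24 h, alpha 0.05, power 0.90. No SD is given, so 86 cannot be reproduced directly. Solving n = 2 × SD² × (z_α + z_β)² / 24² for the SD at n = 86:

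- Two-sided: SD = 24 × √43 / (1.960 + 1.282) = 48.6 h.
- One-sided: SD = 24 × √43 / (1.645 + 1.282) = 53.8 h.

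The same formula run forwards over this range of assumed SDs:

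| Assumed SD | n per arm, two-sided | n per arm, one-sided |
|---|---|---|
| 48 h | 85 | 69 |
| 50 h | 92 | 75 |
| 52 h | 99 | 81 |
| 54 h | 107 | 87 |

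At SD 48 h (a standardised difference of 24/48 = 0.5), the t-based calculation gives 85.03, rounded up to 86, for a two-sided test. It gives 69.2, rounded up to 70, for a one-sided test. A two-sided derivation with SD 48 h therefore matches 86, but an SD near 54 h with a one-sided derivation comes equally close.

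**4. Two-sided power if 86 was derived one-sided (SD 53.8 h)**

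- At 86 per arm: Φ((24/53.8) × √(86/2) − 1.960) = Φ(0.966) = 83.3%.
- At 100 per arm: Φ((24/53.8) × √(100/2) − 1.960) = Φ(1.196) = 88.4%.
- For 90% power: 2 × (3.242 × 53.8/24)² = 105.5, so 106 per arm.

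If 86 was derived two-sided, the stated 90% stands.

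**The case against.** The strongest reply is that the primary outcome is safe. Test, sidedness and level are given for length of stay in two places, and a specific rule ordinarily governs over a general one. The one-sided sentence also closes a paragraph that opens with participant characteristics, so it may have been meant for descriptive comparisons. This largely stands for the primary outcome. It does not protect the secondary outcomes, because the heading includes them and no other threshold is given. Baseline comparisons fall under the one-sided sentence on any reading.

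A reader might also infer that the one-sided rule both doubles the false-positive rate and blinds the tests to robotic harm. The documents do not support that pair. A direction fixed in advance keeps total error at 5%. Total error reaches 10% only if the direction is chosen after seeing the data, and such tests can still flag harm. Blindness to harm requires every test to be fixed in advance towards robotic benefit, which the article does not say. The cited SSO excess was mainly seromas needing no intervention, and serious adverse events go to the monitoring board within 24 h whatever the test. These facts limit the harm argument without removing it as one possible consequence.

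**Conclusion.** The contradiction is real and stands in the text itself. For length of stay the two-sided rule can reasonably be taken to govern, so the exposure lies mainly in the secondary and baseline comparisons. There the only stated threshold is laxer in one direction, 5% instead of 2.5%, without saying which. The two further consequences are alternatives: about 10% total error if the direction is picked afterwards, or no ability to declare excess robotic wound events if all tests are directed at robotic benefit.

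Two stronger inferences should not be drawn. First, an inflated chance of at least one false positive across the secondary outcomes needs the direction-picked-afterwards reading, an assumed number of tests and independence between related outcomes; the article supplies none of these. Second, 86 per arm cannot be called the two-sided figure as a matter of fact. That rests on an SD of about 48 h, which the article does not state. An SD of about 54 h fits a one-sided derivation, and two-sided power would then be 83% to 88% for 86 to 100 per arm.

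**What to change.** Delete the one-sided sentence from the general methods section and put in its place: *All tests are two-sided at the 0.05 level.* This agrees with the primary analysis as already written, and it covers the secondary tests and the optional log-transformed t-test.

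In *Sample size*, state whether the alpha of 0.05 was one- or two-sided and give the SD used. If the derivation was two-sided, nothing else changes. If it was one-sided, restate the 90% power for the two-sided test: about 83% at 86 per arm and 88% at 100 per arm, if the SD was near 54 h.

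The cost is about two sentences, to be settled before the outcome data are analysed. The downside is that borderline secondary results become less favourable: a two-sided p between 0.05 and 0.10 would no longer count as significant.

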### Primary analysis

The primary outcome for this study is length of stay measured in hours. Length of stay will start at the time of surgery start and will end when discharge order is placed. Analysis will be performed using the intent to treat analysis. The comparison in length of stay between two groups will be conducted by using two-sided Wilcoxon ranked sum test with significance level of 0.05. Two sample student’s t-test with log-transfomation would also be considered if we are interested to interpret the length of stay with mean and standard error. Per-protocol analysis will also be done if there’s excessive non-adherence or switching groups during the study. Tipping point analysis will be performed when loss of follow up is anticipated.

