### Eligibility criteria

*Inclusion criteria*:Adults ≥ 18 years old.Midline ventral hernia defects ranging from 7 to 15 cm in greatest width as measured by pre-operative CT scan without Valsalva maneuver.Non-emergent caseBody mass index (BMI) less than or equal to 45Patient deemed either a robotic or an open candidate by the operating surgeon

*Exclusion criteria*:Patients 17 years old or youngerPrisonersEmergent casesBMI greater than 45Hernia defects less than 7 cm or greater than 15 cm in width as measured by pre-operative CT scan without Valsalva

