## Assignment of interventions: allocation

### Sequence generation

Patients will be randomized in a 1:1 ratio using a computer-generated permuted block method with random block sizes. Computer-generated treatment random allocation in REDCap® will randomize robotic or open retromuscular hernia repair in the clinic office after consenting. However, since the scheduling requires prior knowledge of how the surgery will be performed (open or robotic), the operating surgeon will know the randomization arm.

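### The primary length-of-stay test is valid but leaves out site and CT defect width; pre-specifying adjustment is a cheap, modest gain in power and precision

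*Protocol article*

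**What the plan says.** - **Primary test.** The Primary analysis section states: "The comparison in length of stay between two groups will be conducted by using two-sided Wilcoxon ranked sum test with significance level of 0.05". The section on non-adherence and missing data repeats it.
- **Alternative.** A t-test on log LOS "would also be considered if we are interested to interpret the length of stay with mean and standard error". It is also a two-group comparison without covariates.
- **Randomization.** Sequence generation says: "Patients will be randomized in a 1:1 ratio using a computer-generated permuted block method with random block sizes". The article mentions no stratification factor.
- **Site.** Study setting and Recruitment name four centres, so site is known for everyone.
- **Defect width.** Eligibility criteria require: "Midline ventral hernia defects ranging from 7 to 15 cm in greatest width as measured by pre-operative CT scan". Width is therefore measured before randomization in every eligible patient.
- **Secondary scores.** These models include the baseline score and "possibly the surgeon as random effects".
- **Sample size.** "Using an alpha of 0.05, a power of 0.90", and for a 24 h "difference in length of stay, the necessary sample size is 86 patients in each arm"; 100 per arm are to be enrolled. No SD for LOS is given.

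**The concern.** LOS ends when a discharge order is written, and a surgeon must judge when the discharge criteria are met. Practice could differ between centres. The need for a transversus abdominis release is decided during the operation and could depend on defect width, so a wider defect may mean a larger procedure and a longer stay.

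If site or width does predict LOS, the pooled test leaves that variation in the noise. Power is then lower, and an interval for the treatment difference wider, than the same patients could give. If randomization is not stratified by site, some imbalance is also to be expected. In a site with 30 of 200 patients, a split of 19:11 or worse has about a 16% chance (hypergeometric, 100 per arm). Adjustment removes the noise that such imbalance adds.

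What is at stake is efficiency, not validity.

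**Working it through.** **Inputs.** From the article: difference 24 h, power 0.90, 86 per arm (100 enrolled), and two-sided 0.05 as in Primary analysis. (The general methods section instead says "One-sided p-values less than or equal to 0.05 will be considered statistically significant"; that conflict is a separate matter.) Assumed, because the article gives neither: the SD of LOS, and the share of its variance (R²) explained by site and width, taken from 0 to 0.30.

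**Step 1: recover the SD behind the plan's figure.** For two means, n per arm = 2 × (SD/24)² × (1.960 + 1.282)².
- Solving for SD at n = 86: 24 × √(86/2) / 3.242 = 48.55 h.
- At SD = 48 h: 2 × 4 × 10.51 = 84.1, so 85 by the normal approximation; the t-test calculation gives 86.

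The plan's 86 fits a two-sided t-test with SD 48 h, a standardized difference of 0.5. It cannot be confirmed, since the article does not state the SD.

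**Step 2: effect of adjustment by formula.** Residual SD = 48 × √(1 − R²). The 95% half-width is 1.96 × residual SD × √(2/86).

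| Joint R² | n per arm for 90% power | Power, 86 per arm | Power, 100 per arm | Half-width, 86 per arm |
|---|---|---|---|---|
| 0 | 85 | 90.6% | 94.2% | 14.4 h |
| 0.10 | 76 | 93.3% | 96.1% | 13.6 h |
| 0.20 | 68 | 95.6% | 97.7% | 12.8 h |
| 0.30 | 59 | 97.5% | 98.8% | 12.0 h |

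**Step 3: simulation of the rank tests.** The set-up was 4,000 trials per scenario, four unequal sites, normal errors, total SD held constant and a 24 h effect. The rank ANCOVA regresses the ranks of LOS on arm, site and width. Power at 86 per arm, with the gain over the plain Wilcoxon test in points:

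| R² site + width | Wilcoxon | van Elteren by site | Rank ANCOVA |
|---|---|---|---|
| 0 + 0 | 88.3% | 87.6% (−0.7) | 87.9% (−0.4) |
| 0.05 + 0.05 | 88.4% | 89.6% (+1.2) | 91.5% (+3.1) |
| 0.10 + 0.05 | 88.8% | 90.6% (+1.8) | 92.1% (+3.3) |
| 0.10 + 0.10 | 88.9% | 90.6% (+1.7) | 94.1% (+5.2) |
| 0.20 + 0.10 | 88.9% | 93.5% (+4.6) | 95.9% (+7.0) |

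Each power estimate has a standard error of about √(0.88 × 0.12/4,000) = 0.5 point. With no treatment effect, all three tests rejected in 5.0% to 5.1% of trials.

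**Step 4: larger sample and skewed LOS.**
- At 100 per arm with 0.10 + 0.05 and normal errors: 93.2 / 94.3 / 95.7%, gains of 1.1 and 2.5 points.
- With skewed errors and 0.10 + 0.10: 94.2 / 96.8 / 98.1% at 86 per arm (gains 2.6 and 3.9) and 96.6 / 98.2 / 98.8% at 100 per arm (gains 1.6 and 2.2).

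Allowing for simulation error and the shape of the distribution, I take the gain at 86 per arm as roughly 2 to 7 points for the rank ANCOVA and about 1 to 5 for van Elteren, over joint R² from 0.10 to 0.30.

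**The case against.** The best defence is that nothing here is wrong. A two-sided Wilcoxon test suits skewed LOS, needs no model and holds its type I error. This stands, and it limits the point to efficiency.

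Several stronger readings are tempting, and the article does not support them:

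- **That chance imbalance between sites biases the test.** It does not. The type I error of a randomized comparison already allows for such imbalance; adjustment only removes noise.
- **That site and width are shown to drive LOS.** No figure in the article links either to LOS. Common discharge criteria, applied at every centre by a blinded surgeon outside the enrolling team, are likely to narrow site differences. The 7 to 15 cm limits restrict how much width can explain.
- **That the loss is large.** Gains of 7 to 15 points appear only with strong assumed inputs: an 18 h effect, which is not the planned 24 h, and 8 h of stay per cm of width, which is 8 × 8 = 64 h across the eligible range. Those scenarios also add the site and width effects on top of a fixed residual SD of 38 h, so total variance grows and part of the fall in power is not due to omitting covariates.
- **That randomization is unstratified.** A condensed article that names no stratification factor does not show that there is none.
- **That the plan contradicts itself by considering a surgeon effect for the secondary scores.** That wording is tentative and concerns repeated-measures models.

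Two further objections also stand. The 10% attrition is counted at 30 days, whereas LOS is complete at the discharge order, so the number analysed may be close to 100 per arm, where the gain is smaller. And a rank ANCOVA gives a test, not an interval in hours, so the change of test alone does not improve the precision of an estimate in hours.

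**Conclusion.** The point holds as a modest efficiency improvement. The article itself fixes the primary test as unadjusted, so this choice is not merely a detail left to an unseen analysis plan. Two baseline variables that every patient has are left unused.

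At an assumed total SD of 48 h and a 24 h effect, the gain at 86 per arm is roughly 2 to 7 power points with rank ANCOVA for joint R² of 0.10 to 0.30, and less at 100 per arm. If neither variable predicts LOS, the cost is about half a point. A linear adjusted analysis with R² of 0.20 would shorten the 95% half-width from 14.4 to 12.8 h.

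The SD and R² values are assumptions. Without them the direction can be stated with confidence but the size cannot. The primary analysis would remain valid if nothing were changed.

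**What to change.** Before unblinded data are examined, amend the primary analysis as follows:

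1. Name one primary test, two-sided at 0.05: a rank-based ANCOVA of LOS on arm, site and CT defect width (continuous), or at least a van Elteren test stratified by site. The first gains more if width matters.
2. Keep the plain Wilcoxon test as a sensitivity analysis.
3. Because the hypothesis is stated in hours, report an adjusted treatment difference in hours with a 95% confidence interval, for example from a linear model on arm, site and width with a robust or bootstrap interval.
4. If the full protocol does stratify the randomization, include those factors in the primary test.

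The cost is a few sentences and no new data. The downside is a slightly more complex primary test and a trivial loss of power if the covariates do not predict LOS. The article plans no interim looks, so the change can be made credibly if it is dated before results by arm are seen; made afterwards, it would not be credible.
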